### Data sources

The study will constitute secondary analyses of antibiotic prescribing data from NHS England covering the period 2013 to 2018. CCGs were established in England in April 2013 following the Health and Social Care Act 2012.^33^ Data on antibiotic prescribing in primary care at CCG level will be sourced from the NHS England Antibiotic Quality Premium Monitoring Dashboard, which is produced by the NHS Business Services Authority (BSA).^34^ Primary Care prescribing data are publicly available from the NHS BSA website. The dataset contains the number of antibiotic items (STAR-PU) prescribed in each CCG from the financial year 2015/2016 to 2018/2019, with data for October 2018 the latest at the time of this protocol. Data for the period 2013 to 2015 will be mapped to CCG level from the practice-level data.

Practice-level antibiotic prescribing data will be sourced from OpenPrescribing, an Evidence-Based Medicine DataLab project by the University of Oxford. OpenPrescribing publishes monthly antibiotics prescribing data from August 2013, with data for October 2018 the latest at the time of this protocol. Practice-level antibiotic prescribing data from OpenPrescribing is not STAR-PU weighted, so the extracted data will be STAR-PU weighted using figures from the 2013 Item-based age–sex weighting for oral antibacterials^14^ and the number of registered patients in each age–gender category in a practice for each specific month.

Overall, the dataset offers coverage of at least 3 years postintervention given that antibiotic prescribing became a QP priority in March 2015. This will be important in investigating the immediate direct and indirect effects of the QP initiative while giving an insight into the sustainability of the identified effects (if any) in the long-term.

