### Variables

The predictor will be a binary variable indicating the implementation of the QP intervention. The intervention will include all periods after March 2015 when the 2015/2016 QP guidance in England was published, while the control will be periods prior to this. The primary outcome of interest is the rates of antibiotic prescribing at CCG level in England, which will be a continuous variable indicating the number of items (per STAR-PU) prescribed per month.

To account for differences in practice and CCG characteristics that can contribute to variance in antibiotic prescribing, we will be adjusting for the number of general practitioners in each practice (from the NHS Workforce data),^35^ the index of multiple deprivation (from the Department for Communities and Local Government),^36^ prevalence of comorbidities (asthma, chronic obstructive pulmonary disease, diabetes, cancer, chronic kidney disease (from the NHS Quality and Outcomes Framework database)),^37^ the prescribing rate of other non-antibiotic drugs (opioids and benzodiazepines) and seasonal influenza vaccination rate (from PHE).^38^

Mediator variables will be derived from the questionnaire data from a PHE survey,^39^ with 187 of the 209 AMS leads representing CCGs in England and data from other organisations that have evaluated the interventions treated as potential mediators in this study. In the PHE survey, participants were required to complete questionnaire items, which included their adoption of national and local strategies in their respective CCG to enable them to meet QP targets on antibiotic prescribing in primary care. The mediator variables will be binary or continuous variables, indicating the adoption of key interventions and intermediaries that are hypothesised to reflect in the integration of the QP guidance in improving antibiotic prescribing in primary care practices.

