### Statistical analysis

Our first analysis will be an interrupted time series to investigate whether antibiotic prescribing rate in England has changed over time, and how such changes, if any, are associated with the QP implementation in March 2015. This will be conducted using the ordinary least square regression method^41^ to assess whether the 2015/2016 QP establishment resulted in a shift in the level and trend in antibiotic prescribing in primary care in England compared with the period before the intervention. Using the practice-level dataset, a univariate time series with the mean antibiotic items (STAR-PU weighted) prescribed in all primary care practices in England for each month will be conducted using the *ITSA* function on Stata, with post-trend specification to show a postintervention trend. The Cumby-Huizinga general test for autocorrelation will be used for general specification test of serial correlation in the time series data.^42^

A new QP guideline was implemented each financial year with changes in the prescribing rate target and the proportion that improved prescribing constituted in the QP award for each year. Our mediation analyses will investigate the effects of the QP by comparing antibiotic prescribing rate in the financial year before its implementation to each subsequent year postimplementation; as such, our dataset for the mediation analyses will have the control group as the financial year before QP and the intervention group as a specific post-QP implementation year. Three analyses will be conducted for each of the three financial years since QP establishment. This will enable us to compare the effects of the different target levels that have been set over the years and the proportions of the QP award attributed to improvement in antibiotic prescribing.

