### Sensitivity analyses

Sensitivity analyses using dummy implementation dates of 1 to 3 months before and after the actual month each of the QP guidance were published will be conducted to assess the difference between the time the guidance is published and the dissemination of information and development of local arrangements by the CCGs. These analyses will further help to investigate the anticipatory effect of the policy and whether lag in implementation attenuates the effect of the intervention.

Also, we will conduct separate analysis with the outcome variable (antibiotic prescribing rate) as a binary variable (indicating whether each CCG achieved the required rate of reduction in antibiotic prescribing as stated in the QP guidance for each year) to examine whether the classification of the outcome variable based on achievement of QP target influences the results.

Subgroup analyses will be conducted on clusters of primary care practices based on their antibiotic prescribing behaviour (high and low prescribers) and indices of deprivation to examine whether any effect of the QP initiative seen in the overall population is different in subgroups of practices. The top and bottom 20% antibiotic prescribers as of March 2015 will be categorised as high and low prescribers. To address the issue of regression to mean in subgroup analyses, we will build a separate model with categorisation into high and low prescribers based on the mean of the prescribing rate of practices in the last 3 months to March 2015. The use of mean of multiple measures will offer a better estimate of each practice’s true mean before the 2015/2016 QP initiative.^48^ The subgroup analysis based on the indices of deprivation data^36 49^ at primary-care practice level will be important in establishing the equity impact of the QP initiative.

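### The interrupted time series has no seasonal term and an unbalanced 20-month pre-QP window, so a winter prescribing peak biases the estimated change towards a QP reduction

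*Protocol article*

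**What the plan says.** The Statistical analysis section of the protocol article opens with an interrupted time series. Its purpose is to see whether the QP "resulted in a shift in the level and trend in antibiotic prescribing in primary care in England compared with the period before the intervention". The estimator is ordinary least squares and the data are "a univariate time series with the mean antibiotic items (STAR-PU weighted) prescribed in all primary care practices in England for each month". One diagnostic is named: "The Cumby-Huizinga general test for autocorrelation will be used for general specification test of serial correlation in the time series data".

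The dates come from two other sections. Under Data sources, "OpenPrescribing publishes monthly antibiotics prescribing data from August 2013, with data for October 2018 the latest at the time of this protocol". Under Variables, "The intervention will include all periods after March 2015 when the 2015/2016 QP guidance in England was published", with earlier periods as control.

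The Sensitivity analyses section adds "dummy implementation dates of 1 to 3 months before and after the actual month each of the QP guidance were published", partly to "investigate the anticipatory effect of the policy and whether lag in implementation attenuates the effect of the intervention".

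The article mentions no month terms, harmonics, deseasonalising or whole-year pre-period. Season appears only in the influenza vaccination covariate, which is there to adjust for differences between practices and CCGs.

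**The concern.** Antibiotic prescribing in primary care plausibly peaks in winter. The Introduction names respiratory conditions as a source of unnecessary prescribing, and influenza vaccination is on the covariate list. A model with only a level and a trend must absorb such a cycle into those terms or into the residual.

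The pre-QP window makes this matter. August 2013 to March 2015 covers August to March twice and April to July once. It begins near the seasonal low and ends soon after the high, so a straight line through it slopes upward even if nothing is changing. Projected past March 2015, that line overstates what would have happened without the QP, and the shortfall is credited to the QP.

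At stake is the size of the QP effect reported by the study's first analysis, and the interpretation of any dummy-date or subgroup series built on the same model.

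**Working it through.** The protocol states no expected effect for this analysis, so there is no figure to reproduce. The check builds the stated design and gives it a series with no QP effect.

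**Inputs from the protocol article**
- Series: August 2013 to October 2018 = 5 + 12 + 12 + 12 + 12 + 10 = 63 months (Data sources).
- Break: first post-QP month April 2015 (Variables). Pre-QP 5 + 12 + 3 = 20 months; post-QP 63 - 20 = 43.
- Targets: reductions of 1% (2015/2016) and 4% (2016/2017) (Introduction).

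**Assumptions not in the documents**
- A stable annual cycle with amplitude A of 5% to 20% of the mean. A = 10% means a peak 10% above the mean and a trough 10% below.
- A cosine peaking in December, January or February, plus two non-cosine winter shapes at 10%.

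**Model.** y(t) = b0 + b1·t + b2·P(t) + b3·P(t)·(t - t0), where P = 1 from April 2015 and t0 is April 2015. Least squares is linear in y. The cycle s(t) therefore adds (X'X)⁻¹X's to the coefficients, whatever the true effect, and this scales with A.

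**False level change b2, % of the mean, zero true effect**

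| Peak | A = 5% | 10% | 15% | 20% |
|---|---|---|---|---|
| December | -1.9 | -3.9 | -5.8 | -7.7 |
| January | -2.5 | -4.9 | -7.4 | -9.8 |
| February | -2.3 | -4.6 | -7.0 | -9.3 |

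The two non-cosine shapes give -3.3% and -6.0% at A = 10%.

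**False trend change b3 at A = 10%.** December -0.9%, January -3.3%, February -4.7% per year. For the January peak the fitted post-QP slope is zero, so the whole -3.3% is the false upward pre-QP slope (about 0.27% per month). Twelve months after the break, the combined false reduction is 4.9 + 3.3 = about 8.2%.

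**Significance.** With seasonality alone, p for the level change at the April 2015 break is 0.13 to 0.46 across ordinary, heteroscedasticity-robust and Newey-West errors. With autoregressive noise added (assumed SD 3%, correlation 0.2; January peak), a significant false drop appears in about 10% of runs at A = 5% and in under 4% at A = 10% to 15%, because the unmodelled cycle inflates the residual variance.

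**With a real effect.** For a true step of -4% and a January peak, the expected estimate is -4 - 2.5 = -6.5% at A = 5% and -4 - 4.9 = -8.9% at A = 10%. At A = 15%, simulated detection falls from about 62% with month terms to below 40% without them.

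**Dummy dates, A = 10%, zero effect: false level change (%) by shift in months**

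| Peak | -3 | -2 | -1 | 0 | +1 | +2 | +3 |
|---|---|---|---|---|---|---|---|
| December | -0.6 | -3.1 | -4.3 | -3.9 | -2.1 | +0.5 | +3.2 |
| January | +1.6 | -1.5 | -3.8 | -4.9 | -4.5 | -2.8 | -0.2 |
| February | +3.4 | +0.6 | -2.4 | -4.6 | -5.7 | -5.2 | -3.5 |

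The estimate follows the calendar month of the break.

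**After the fix.** With calendar-month indicators or one annual sine and cosine pair, the false level and trend changes for the cosine cycles are zero.

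**The case against.** **This is a condensed article, and month terms may sit in a fuller plan.** They may. In some usage, univariate means only that there is a single series, which does not forbid deterministic seasonal terms. But the article does more than stay silent: it names the estimator, the terms of interest, the series and the diagnostic. Followed as written, that model gives the bias shown. A serial-correlation test may flag the cycle, but no consequence is attached to it, and robust standard errors leave the coefficients unchanged.

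**A reader might infer that the plan would produce a significant false QP effect.** The check does not support that. Seasonality alone rarely reaches significance here. The problem is a biased effect size, with lost power at larger amplitudes.

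**A reader might also infer that the dummy dates would appear to confirm a QP effect at the true date.** That fails too. The false drop is largest at April 2015 only for a January peak; it is largest at March for December and at May for February. It often fades or reverses by three months, which an alert analyst could take as a warning. The article also does not say that these dates are applied to this series. What stands is conditional: if they are, they cannot tell seasonality from anticipation or lag.

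**The time series is preliminary to the mediation work.** This is true and limits the reach. The mediation analyses compare financial years, which are balanced by calendar month.

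**The size rests on an assumed cycle.** This stands. The direction of the level bias was the same for every winter shape tried; its size cannot be fixed from the documents.

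**Conclusion.** The concern holds as a bias in the interrupted time series estimates. The stated model has no seasonal term, and its 20-month pre-QP window is unbalanced across the calendar. Under a winter-peaking cycle, the level change is pushed towards a QP reduction by about 2% at 5% amplitude and up to about 10% at 20%. That exceeds the 1% target throughout and is close to or above the 4% target from about 10% amplitude. The trend change is also pushed downward materially in most scenarios, but only slightly for a December peak. The bias adds to whatever the QP really did.

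This rests on a stable annual cycle peaking between December and February, an assumed amplitude of 5% to 20%, and April 2015 as the first post-QP month. It does not show that a significant result would arise from seasonality alone, that the dummy dates would corroborate one, or that the mediation results are biased in the same way.

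**What to change.** Add calendar-month indicators, or one or two annual harmonic pairs, to the segmented regression, and report autocorrelation-robust standard errors such as Newey-West. State this in the Statistical analysis section. Use the same terms in any dummy-date or subgroup time series, so that a shift in the break date is not also a shift in season.

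The data already held are enough: 63 months give every calendar month at least five times. The cost is 2 degrees of freedom for one harmonic pair, 4 for two pairs, or 11 for month indicators. Residual degrees of freedom fall from 63 - 4 = 59 to 57, 55 or 48. The terms assume the same seasonal pattern before and after the QP, so an unusually severe or mild winter would remain in the residual.

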Interventions such as antibiotic stewardship programmes, education and training initiatives targeted at prescribers and patients, financial incentives, among others have been implemented in England to reduce AMR through reduced prescribing. In particular, the Quality Premium (QP) is a National Health Service (NHS) England initiative established in 2013 to reward Clinical Commissioning Groups (CCGs) financially based on the quality of specific health services considered to be of national or local priority and commissioned over a specific period.^17^ Improvement of antibiotic prescribing in primary care was one of the national priorities in the 2015/2016 guidance,^18^ constituting 10% of the premium awarded from 2016/2017 to date.^19 20^ Key aspects of the ‘improved antibiotic prescribing’ priority are reductions in the number of antibiotics prescribed in primary care facilities across England and in the proportion of broad-spectrum antibiotics prescribed in primary care (2015–2017).^19^ Part of the requirements in the 2015/2016 QP guidance for demonstrating improved antibiotic prescribing by CCGs was a reduction in the number of antibiotics prescribed in primary care by 1% of the mean value in England in 2013/2014 (ie, 1.61 items per Specific Therapeutic group Age-sex Related Prescribing Unit (STAR-PU)). This was further increased to 4% in the 2016/2017 guidance.

Emerging evidence suggests a reduction in antibiotic prescribing in primary care practices in the UK following the QP initiative.^21 22^ Prescribing data from England show a reduction of about 2.7 million antibiotic items between 2014/2015 and 2016/2017 financial year.^23^ Eighty-eight per cent of the CCGs in England achieved the target of reducing antibiotic prescribing in the first 2 years of QP.^21^ Also, there has been a significant reduction in the proportion of broad-spectrum antibiotics prescription with 83% of the CCGs meeting their target in the first 2 years.^21^ Such reductions in antibiotic prescribing would be expected to contribute to reductions in the development of resistance.^24^ However, little is known about the mechanisms by which the QP initiative impacted on antibiotic prescribing in primary care practices.

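### The year-by-year mediation contrasts have no stated adjustment for a pre-QP trend, so uncaptured drift would enter the total and direct effects, and they cannot show the effect of target level or award share

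*Protocol article*

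**What the plan says.** The Statistical analysis section of the protocol article estimates the QP effect in the mediation models by "comparing antibiotic prescribing rate in the financial year before its implementation to each subsequent year postimplementation". Each dataset has "the control group as the financial year before QP and the intervention group as a specific post-QP implementation year". It adds that "Three analyses will be conducted for each of the three financial years since QP establishment", which I read as one analysis for each of three years. The stated purpose is: "This will enable us to compare the effects of the different target levels that have been set over the years", and likewise the share of the award tied to antibiotic prescribing. Under Variables, "The predictor will be a binary variable indicating the implementation of the QP intervention".

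The mediation models adjust for the characteristics listed under Variables: GP numbers, deprivation, chronic disease prevalence, opioid and benzodiazepine prescribing, and influenza vaccination. Neither calendar time nor a pre-QP slope is named. The pre-QP trend is modelled only in the separate interrupted time series, a single national monthly mean built from practice data. Nothing says that its slope is carried into the mediation models.

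On targets, the Introduction gives a 1% reduction for 2015/16, relative to a 2013/14 mean of 1.61 items per STAR-PU, and then: "This was further increased to 4% in the 2016/2017 guidance". It gives no target for the third year. On award share it describes the antibiotic element as "constituting 10% of the premium awarded from 2016/2017 to date" and gives no share for 2015/16.

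**The concern.** Within each two-year dataset the exposure indicator and the financial year are the same variable. A change between the two years that is not due to QP, and that the covariates do not track, is therefore counted as a QP effect. The time series guards against this; the mediation analyses, as described, do not. Yet the Study aim and objectives section asks for direct, indirect and total effects, and the mediation analyses supply that decomposition.

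Two conclusions are at stake. The first is the size of the total and direct effects, and with them the proportion mediated. The second is the comparison across target levels. Bias that grows with elapsed time can look like a graded response, because the later year with the higher documented target is also the year with more accumulated drift.

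**Working it through.** The document gives no effect estimate or power figure for the mediation analysis, so there is nothing of its own to reproduce. The check is algebra, followed by a simulation.

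**Inputs from the article.** Control is the financial year before QP (2014/15, inferred from publication in March 2015). There are three later years, whose midpoints lie 1, 2 and 3 years after the control midpoint. Baseline is 1.61 items per STAR-PU. Targets are 1% (0.01 x 1.61 = 0.0161 items) and 4% (0.04 x 1.61 = 0.0644 items). Practice data start in August 2013.

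**Assumption.** The drift d is not in the document, so a range is shown. It is taken as linear, common to all CCGs and not absorbed by the covariates.

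**Step 1, total effect.** With no QP effect, the mean of post-QP year k minus the mean of the control year is k x d. Figures are percent of 1.61, with items per STAR-PU in brackets:

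| Assumed d per year | Year 1 | Year 2 | Year 3 |
|---|---|---|---|
| -0.5% | -0.5% (-0.008) | -1.0% (-0.016) | -1.5% (-0.024) |
| -1% | -1% (-0.016) | -2% (-0.032) | -3% (-0.048) |
| -2% | -2% (-0.032) | -4% (-0.064) | -6% (-0.097) |

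At -1% a year, drift alone equals the 2015/16 target in year 1. At -2% a year, it equals the 4% target in year 2. A positive d reverses the sign: with d = +1% and a true effect of -1% in every year, the contrasts would read 0%, +1% and +2%.

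**Step 2, where the bias goes.** The simulation used 209 CCGs, annual totals of 12 seasonal monthly values, d = -1%, one covariate, and a mediator absent before QP and adopted by about half of CCGs afterwards; 500 runs per scenario.

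- No QP effect: total -1.00%, -2.00%, -3.01%; direct -0.96%, -2.03%, -2.99%; indirect within 0.04 percentage points of zero.
- True mediated effect of about -0.5%, no true direct effect: the indirect estimate stays at -0.49%, -0.50%, -0.48%. The proportion mediated should be 1 but comes out at 0.33, 0.20 and 0.14. By formula: 0.5/(0.5 + 1) = 0.33, 0.5/(0.5 + 2) = 0.20, 0.5/(0.5 + 3) = 0.14.

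**Step 3, can a two-year dataset carry a trend term?** Number the months t. For calendar month m of the financial year and exposure X (0 or 1), t = m + 12kX. Once calendar-month terms and X are in the model, t is an exact linear combination of them, so a linear trend cannot be estimated alongside both. More pre-QP months are needed. August 2013 to March 2015 gives 5 + 12 + 3 = 20 months, in which eight calendar months (August to March) occur twice.

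**Step 4, target level.** There are three contrasts and one shared control year. Between years 1 and 2 the target goes from 1% to 4%, elapsed time from 1 to 2 years and drift from d to 2d, all together. From 2016/17 the award share is 10% throughout, so years 2 and 3 do not differ on it.

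**The case against.** The strongest reply is that the comparison is not a raw difference. It is covariate-adjusted, and opioid and benzodiazepine prescribing or influenza vaccination could absorb part of a general drift. That stands: only drift the covariates miss is credited to QP.

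A condensed article may also leave model terms to a fuller plan, and monthly outcomes give 24 points per dataset, so a time term might be intended. That stands in part. The article does not rule one out, but Step 3 shows that it could not be combined with calendar-month terms in the two-year datasets the article fixes.

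A reader might infer that the study's mediation findings are invalid. The document does not support that. A trend common to all CCGs leaves the indirect effect largely intact when the mediators are absent before QP, vary between CCGs afterwards and do not themselves trend.

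A reader might also infer that the effects are known to be biased downward, or that drift would reproduce the sequence of targets. Nothing in the article gives the existence, size or direction of a pre-QP trend. Only two targets are stated, and none of the drifts illustrated gives 1% followed by 4%. Nor can the award share be called constant throughout, because the 2015/16 share is not given and the article says the share changed.

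Finally, the Limitations section already concedes limited causal inference and unmeasured confounding. It names consultation rate but not secular trend, and shifting the start date by 1 to 3 months in the Sensitivity analyses does not remove one.

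**Conclusion.** The point holds in a bounded form. As described, the yearly mediation contrasts adjust for characteristics but not for a pre-QP trend. Residual drift would enter the total and direct effects in proportion to years elapsed (d, 2d, 3d) and distort the proportion mediated. At an assumed -1% a year that means -1%, -2% and -3% with no QP effect at all. This rests on a linear, CCG-common drift whose size and sign are assumed; with no trend there is no such bias, and with a rising one an effect would be masked.

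The target-level conclusion fails regardless of the size of the drift. Target, time since start and accumulated drift change together over three contrasts with one control year, so the effect of target level or award share is not identified.

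**What to change.** 1. Delete the statement that the yearly analyses compare target levels or award proportions, and label the results year 1, year 2 and year 3 since QP.
2. Add a CCG-level outcome model using all pre-QP months (August 2013 to March 2015) with time and calendar-month terms, giving each post-QP year as a departure from the projected trend. Report it beside the year contrasts.
3. Interpret the total and direct effects causally only where the two analyses agree, and state beforehand what counts as agreement. Treat the proportion mediated with the same caution.

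The cost is plan wording and one more model on data already due to be assembled, since the article maps the 2013 to 2015 practice data to CCG level.

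The drawbacks are real. Intervals will be wide, especially in year 3, because a 20-month slope is projected up to three years ahead. The slope may also carry part of the effect of the Chief Medical Officer's letter, itself a hypothesised mediator. It began in September 2014, so of the eight calendar months seen twice before QP, seven (September to March) have their second value in or after that month. For that reason the trend model should stand beside the year contrasts and not replace them.

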### Study aim and objectives

Using routinely collected population-level data on antibiotic prescribing in England, this study aims to address the research question: What are the mechanisms and mediators of the impact of a high-cost health-system level intervention, the ‘antibiotic prescribing quality premium’? We will investigate the difference in antibiotic prescribing rate pre-QP and post-QP initiative to establish its direct, indirect (through mediators) and total effects in reducing antibiotic prescribing in primary care practices in England.

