## Limitations

This study has some limitations. The survey that provided data on mediator variables included 187 of the 209 CCGs existing at the time of the study. However, this sample size is large enough for strong statistical power, and multiple imputation will be used to address issues on missingness. Furthermore, due to the limited data on practice-level interventions or strategies that might potentially mediate the effect of the QP on antibiotic prescribing, we will not be able to extensively investigate the mechanism of QP impact at the practice level. Nevertheless, extensive investigations will be conducted at CCG level where we have more data on potential mediators.

In 2013, the Primary Care Trusts in England, which were responsible for planning and commissioning healthcare services at the primary care level, were transformed to CCGs.^50^ As such, our investigations are restricted to the CCG era. This is important as the QP initiative is implemented and rewards paid out at CCG level.

We recognise that the causal interpretation of any effect from our mediation analysis rests on assumptions such as sequential ignorability and exchangeability. Causal inference from this analysis will be limited given that our data are observational with the absence of random assignment of cases to treatment and mediator levels, as well as the likelihood of unmeasured confounders. The rate of consultation for conditions where antibiotics might be prescribed is one of the unmeasured confounders in our study. This has not been accounted for in our analyses as these data are not available nationally at the practice level.

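### In each mediation analysis QP exposure is the same thing as calendar year for every CCG, so CCG-based intervals for the total and direct effects omit national year-to-year variation

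*Protocol article*

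**What the plan says.** In the protocol article, Variables, the exposure is a single indicator: "The predictor will be a binary variable indicating the implementation of the QP intervention". Its switch date is national: "The intervention will include all periods after March 2015 when the 2015/2016 QP guidance in England was published". Under Statistical analysis, the mediation dataset "will have the control group as the financial year before QP and the intervention group as a specific post-QP implementation year", and "Three analyses will be conducted for each of the three financial years since QP establishment". I read this as one contrast per post-QP year, all against the same pre-QP year. The section says these contrasts will be used to compare the different yearly targets.

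Study aim and objectives promises "to establish its direct, indirect (through mediators) and total effects in reducing antibiotic prescribing". The mediation work sits mainly at CCG level (Limitations: "extensive investigations will be conducted at CCG level where we have more data on potential mediators"), with mediator data from "187 of the 209 AMS leads representing CCGs in England". On the size of that survey, Limitations says "this sample size is large enough for strong statistical power".

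A separate interrupted time series of the national monthly mean, with a test for autocorrelation, is planned as the first analysis.

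**The concern.** No CCG starts QP later or stays unexposed, so within any one mediation analysis the exposure has one unit on each side: a year. Whatever moves a whole year for all CCGs (an infection season, a national campaign, a coding change) appears alike in every row of that year and is fully collinear with the QP indicator. Standard errors computed from CCG rows describe variation between CCGs, and two years leave no degrees of freedom for variation between years.

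The confidence intervals and p-values for the total and direct effects, and the denominator of any proportion mediated, would then be read as evidence that QP changed prescribing when they do not carry the relevant uncertainty. The ranking of the yearly targets is affected in the same way.

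**Working it through.** **Nothing to reproduce.** The article gives no SD, standard error, alpha or power figure for these models, so the check uses stated assumptions.

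**From the protocol.** 187 CCGs with mediator data (Variables). A national mean of 1.61 items per STAR-PU in 2013/2014, taken here as an annual rate, with reduction targets of 1% and then 4% (Introduction). These are 0.01 × 1.61 = 0.0161 and 0.04 × 1.61 = 0.0644.

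**Assumed.** Two-sided 5%; no QP effect and no trend; one row per CCG-year; uncorrelated national year shocks with SD *s* (% of the mean), being what is left after covariate adjustment. SD of a CCG's yearly change 4% or 6%. Residual SD 10% or 15% if rows are treated as independent.

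**Formulas.**
- Sampling error from CCGs: SE_CCG = SD_change/√187.
- True SE of the year difference = √(SE_CCG² + 2s²).
- SE reported by the model: SD_change/√187 if paired by CCG, or SD_resid × √(2/187) if rows are treated as independent. In the independent case SE_CCG uses SD_change 4%.
- False-positive rate = 2 × [1 − Φ(1.96 × SE_model / SE_true)].

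**One case in full.** Paired, SD_change 4%, s = 1%: SE_model = 4/√187 = 0.29%; SE_true = √(0.29² + 2 × 1²) = 1.44%; 1.96 × 0.293/1.444 = 0.40; rate 69%.

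**False-positive rate, total effect.**

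| Model SE | s = 0 | s = 1% | s = 2% | s = 3% |
|---|---|---|---|---|
| Paired, SD of change 4% | 5% | 69% | 84% | 89% |
| Paired, SD of change 6% | 5% | 56% | 76% | 84% |
| Independent rows, residual SD 10% | 0% | 16% | 48% | 63% |
| Independent rows, residual SD 15% | 0% | 4% | 29% | 48% |

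The independent-row rates are lower only because that SE ignores the pairing of CCGs and is too large for the CCG part of the error.

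**Direct and indirect effects.** A single-mediator regression was simulated 3,000 times per setting (between-CCG SD 0.20, within-CCG SD 0.05 items per STAR-PU; mediator adopted by 20% of CCGs in the pre-year and about 60% in the post-year). With errors clustered by CCG, the direct effect was falsely significant in 5%, 16%, 37%, 61% and 73% of runs at s = 0, 0.5, 1, 2 and 3%. With unclustered errors the figures were 0%, 1%, 8%, 33% and 50%. The mediator-to-outcome coefficient stayed at 5.4% throughout. An indirect effect also needs the exposure-to-mediator shift. That is again one year against another, so a national change in uptake unrelated to QP enters it in the same way. The simulation did not test that path.

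**Shared pre-QP year.** Two contrasts each have year variance 2s² and share covariance s², a correlation of s²/2s² = 0.5. In simulation with CCG-clustered errors and s = 1%, all three were falsely significant together in 34% of runs, against 0.4% at s = 0.

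**Against the targets.** With within-CCG SD 0.05, the CCG-based 95% half-width is 1.96 × √(2 × 0.05²/187) = 0.010 items per STAR-PU. Adding 2s² under the root gives 0.025, 0.046 and 0.090 at s = 0.5%, 1% and 2%. At 1%, a change equal to the first target (0.0161) lies inside the half-width. At 2%, so does one equal to the second (0.0644).

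**The case against.** Four points deserve weight.

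1. *The plan already turns to the time series for overall change.* This is largely right, and it is why the remedy is modest. But the objectives also promise total and direct effects, and the error of the time series does not enter the mediation intervals. The date shifts of 1 to 3 months under Sensitivity analyses do not reach year-level variation either.

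2. *Limitations already concedes unmeasured confounding and limited causal inference.* It does, and a national shock can be seen as a time confounder. That caveat concerns bias and does not tell the reader that the intervals are too narrow. The listed covariates, influenza vaccination among them, may absorb part of a year difference, so *s* must be read as a residual SD.

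3. *The power sentence answers survey non-response.* In context this is fair, and the sentence does not claim precision for the year contrast. It is, however, unqualified, and its reach should be stated.

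4. *The size is assumed.* It is. A reader might infer that the mediation models will usually produce false QP effects. The documents do not support that unconditionally: they give neither the year-to-year SD nor the standard-error method, and with independent rows and an SD of 1% or less the rate can be at or below nominal.

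A reader might also infer that adding 2s² to the variance repairs the intervals. It cannot be the main remedy. Practice-level data start in August 2013 (Data sources), about 1.7 years before QP. Later years mix year variation with changing QP targets, and the term assumes uncorrelated year shocks.

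**Conclusion.** The structural point follows from the protocol alone. With one pre-QP and one post-QP year and a simultaneous national start, CCG rows contain no information on year-to-year variation. Intervals and p-values for the total and direct effects therefore leave it out, however many CCGs contribute. How much this matters is conditional: with a residual year SD of 1–3% of the mean and no QP effect, false positives for the total effect run at about 56–89% with CCG-paired errors and about 4–63% with independent rows. Agreement among the three yearly contrasts is not independent confirmation.

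A reader might infer that indirect effects are safe because a common shift is absorbed by the exposure coefficient. That holds only for the mediator-to-outcome coefficient. Nor does the point invalidate the time series, although that series is itself short before QP.

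**What to change.** In Statistical analysis:
- State that inference on whether, and by how much, prescribing changed with QP comes from the national interrupted time series, with standard errors adjusted for serial correlation.
- Report the CCG-row total and direct effects, and any proportion mediated, with intervals labelled as conditional on the two years compared. Do not use their p-values to claim a QP effect or to rank the yearly targets.
- Limit unqualified CCG-based inference to the mediator-to-outcome association.
- As a sensitivity display only, show how the total and direct intervals widen for assumed year SDs of about 0.5–3%.

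In Limitations, say that the 187 CCGs give power for between-CCG mediator contrasts and not for the year contrast.

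This costs wording and one display, with no new data. The price is wider or more qualified statements on the total and direct effects.
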